### Power calculations

We have conducted power calculations for the majority of the secondary and exploratory outcomes (Table 3). Based on unpublished calculations of 176 to 263 previous patients with eating disorders in routine care at Stolpegaard Psychotherapy Centre, the SDs of their post-treatment responses to SCL-90-R and WHO-5 were used. Since the EDE, ORS and SDS are not previously used at Stolpegaard Psychotherapy Centre, power calculation is based on norms from previous studies [55-57].

**Table 3 T3:** Power calculations

**Outcome**	**Minimal relevant difference (points)**	**SD (points)**	**Risk of type I error**	**Power (N = 128)**	**Power (N = 170)**
Eating Disorder Examination (EDE)	0.5	1.33	5%	55.9%	68.3%
Outcome Rating Scale (ORS)	4.5	9.5	5%	75.8%	86.7%
Symptom Check List (SCL-90-R)	0.3	0.67	5%	71.0%	82.8%
WHO-Five Wellbeing Index (WHO-5)	2.5	5.6	5%	70.8%	82.5%
Sheehan Disability Scale (SDS)	3.5	7.1	5%	79.1%	89.2%

### Statistical analysis plan

The analyses are intention–to-treat analyses using a two-sided significance test at 5%. All analyses will be conducted blinded with the two intervention groups coded as A and B.

### Outcomes

The primary outcome is the rate of attendance. It is defined as the number of group sessions the patient has attended over the number of planned sessions (20 or 25 sessions). If at group session # n (n <20) the therapist decides that the patient needs not attend further sessions, the number of planned sessions is set equal to n. When a patient discontinues treatment early, the therapists decide whether this is in accordance with the treatment plan (categorized as ‘planned withdrawal’ or ‘unplanned withdrawal’).

In the analysis of the rate data, the model fit of a Poisson model and a negative binomial model both with offset equal to log (number of planned sessions) are compared and the best fitting model is chosen provided it fits the data reasonably well. In the analysis of continuous outcomes the univariate general linear model is used. If the assumptions of a regression are not fulfilled, a non-parametric test is used (Mann-Whitney).

All outcomes are analyzed using regression analyses, including the binary intervention indicator. The primary results are those adjusted by the protocol-specified stratification variables and (where measured) the baseline value as covariates. In an exploratory analysis the analyses will be repeated with the categorical variable ID-group (identity code of the group) as an additional covariate, and it will be tested if the outcome depends on the treatment group. Then it will be tested if ID-group and the intervention indicator interact. If so, subgroup analyses of the various treatment groups will be conducted.

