### Therapists

Fifteen therapists are participating in the trial, three male and twelve female (mean age = 44.3 years, SD 9.1). Their general average experience with psychotherapy is 7.2 years (SD 6.6), and their average experience with the treatment of eating disorders is 3.8 years (SD 5.2).

As part of the clinical routine, the therapists have case supervision in groups with team colleagues every other week, lasting one and a half hours. The supervision format is systemic and narrative, structured around the idea of ‘reflecting teams’ [28].

Before data collection began, the therapists had two training sessions (three hours each) in feedback-informed clinical work, led by an external certified FIT trainer and associate at the International Center for Clinical Excellence [20]. The therapists were introduced to the method and instructed in the use of the measures in clinical practice [17]. Only two had worked with FIT in previous jobs. Each therapist was placed in both a control group and an experimental group and thus provided both treatments. To ensure that the therapists followed the feedback method and to reinforce the implementation process, the training was supplemented with one and a half hour hour monthly FIT supervision during the data collection period.

The therapists were assumed to be following the feedback method adequately after this, with no further control for adherence to the method. Because of the lack of published guidelines for the use of feedback in group therapy, the therapists were encouraged to use the feedback according to the guidelines for individual therapy [17]. In cases where these guidelines were insufficient, the supervisor was involved.

Immediately after the second training session with the FIT trainer, the therapists answered an attitude survey ([name]; allegiance measure; unpublished data) asking if they believed working with GSRS and ORS would make a positive difference in their therapeutic work. All therapists agreed that it would improve their clinical work. This therapist allegiance can potentially positively influence the results and exaggerate an effect of feedback on outcome. In order to investigate if the first attitude survey was influenced by the ‘rush’ after the training session, we asked the therapists again before they started using the method. The answers were the same in the second survey ([name]; allegiance measure; unpublished data).

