### Outcomes

The primary outcome is treatment attendance in the intervention period, defined as a rate (number of attended therapy sessions divided by the number of planned therapy sessions). If a patient ends therapy prematurely, and this is in accordance with the therapists, the number of attended sessions will be set equal to the planned number of sessions. The secondary outcome is the global score of eating disorder examination (EDE) interview, assessed at the end of intervention. The mean score in the two intervention groups are compared.

The exploratory outcomes are: ORS, the Symptom Check List (SCL-90R), the Sheehan Disability Scale (SDS), the WHO-Five Wellbeing Index (WHO-5), and suicide and self-harm.

For all outcomes except the ORS, the scores obtained in the two intervention groups after the end of the treatment are compared. With regard to the ORS, the last available score for each patient in the two groups is compared (see further description of these outcomes below).

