### Randomization and blinding

The Copenhagen Trial Unit (CTU) will be responsible for the central randomization. They have no clinical involvement in the trial. Randomization is carried out according to a computer-generated allocation sequence with a varying block size kept unknown to the investigators. After each patient is assessed to be eligible for the trial, the trial secretary will call CTU, provide a personal pin code and receive the randomization result.

The randomization is stratified for eating disorder diagnosis (BN, EDNOS or BED) and treatment type (basic or elaborate). Patients and therapists are naturally aware of the patient allocation but secondary outcome assessment (EDE), statistical analyses, and drawing of conclusions will be done with the blind intact. Blinding is maintained by instructing the intervention team to withhold patient information from the research team. The research team has no clinical contact with the patients from assessment to end of intervention, and the assessors have no knowledge about the patient’s randomization status at the end of intervention. In order to prevent the risk of bias, such as when therapists are assessing patient withdrawal, we have a blinded assessor counting the attendance rate and checking each patient’s medical file. In order to prevent actual bias, the research team is not present in supervision or when the therapists are discussing patients at conferences.

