## Discussion

Attendance to psychotherapy is a prerequisite for the therapy to have an effect. However, a large proportion of patients end treatment prematurely, which has been associated with poorer treatment outcomes [5,6]. In this trial, we hypothesize that integrating patient feedback in the psychotherapy process will increase attendance and patient outcome. This is the first randomized trial of the effect of feedback on group psychotherapy for patients with eating disorders. Below, we discuss some of the potential limitations and strengths of the F-EAT trial.

The trial is subject to at least four potential limitations. First, although the trial was designed in order to minimize the risk of bias [58-60] and the risk of random errors [58], most outcomes are at risk of being assessed with some bias, as only the secondary outcome measure (EDE) is possible to blind [58-60]. Previous research has indicated that non-blinded assessors tended to be more optimistic about patient outcome when compared to blinded assessors [61]. Blinding is thus used whenever possible and data will be analyzed according to the intention-to-treat principle. We employed central randomization with an allocation sequence stratified for prognostic factors [58-60].

Second, the therapists are trained and supervised by an engaged trainer and became excited about the feedback method. The trainer is the only certified trainer in Denmark and is herself involved in the ICCE. It is possible that, as she believes in the benefits of feedback, this might influence the therapist allegiance. The potential allegiance bias was part of our considerations beforehand, however it was important to us that the therapists received proper training and continuing supervision in the feedback method. The alternative would be to collaborate with a less experienced trainer and/or have less training. This solution could imply that the therapists failed to comply with the method or refused to use it, and would pose a greater risk to the trial overall since it would compromise data collection.

Third, the fact that most therapists provide treatment both in an experimental and a control group can cause a contamination between the groups. However, neither the participants nor the therapists in the control groups are informed of the patients’ progress, and we therefore hypothesize that any contamination will be minor.

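### Therapists who know the allocation label early endings as planned or unplanned, and the label moves the primary outcome; the blinded assessor is not said to make or overrule it

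*Protocol article*

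**What the plan says.** The primary outcome is sessions attended divided by sessions planned, with 20 or 25 planned according to diagnosis. Early endings have a special rule, and the article gives it in two forms.

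- **Outcomes (Methods/design).** If the therapists agree with the early ending, "the number of attended sessions will be set equal to the planned number of sessions".
- **Outcomes (statistical analysis plan).** If at session n, with n below 20, "the therapist decides that the patient needs not attend further sessions, the number of planned sessions is set equal to n". For any early discontinuation, "the therapists decide whether this is in accordance with the treatment plan", and the ending is recorded as a planned or an unplanned withdrawal.

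On who knows what:

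- **Randomization and blinding.** "Patients and therapists are naturally aware of the patient allocation". The same section names therapists' assessment of withdrawal as a source of bias and answers that "we have a blinded assessor counting the attendance rate" and checking the medical file.
- **Discussion.** Most outcomes are at some risk of biased assessment, "as only the secondary outcome measure (EDE) is possible to blind".
- **Therapists.** Each therapist treats in both arms. On the value of the feedback scales, "All therapists agreed that it would improve their clinical work". The article adds that this allegiance could exaggerate an effect.

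**The concern.** Counting sessions is the objective part of the outcome. The subjective part is deciding whether an early ending was agreed, and the statistical section leaves that decision with people who know the arm and expect one arm to do better. Because each therapist works in both arms, the same person can apply a different standard in each. The information behind the decision also differs by design: therapists see progress graphs and alerts in the feedback arm, while the control arm's forms stay sealed until analysis.

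Coding the arms as A and B at analysis cannot undo a label assigned earlier with knowledge of the arm. If labelling differs between arms, the primary test can reject with no true difference in attendance. Under the ordered testing in the Multiplicity section, that rejection would also open the test of the EDE score.

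**Working it through.** **1. The plan's own figure.** With a difference of 3 sessions, SD 6 and two-sided 5%, n per arm = 2 × (1.96 + 0.842)² × 6²/3² = 62.8, so 63 by the normal formula. With the t distribution, 64 per arm gives 80.1% power. For 90% power, 2 × (1.96 + 1.282)² × 4 ≈ 84.1, so 85 per arm. The stated 64 and 85 reproduce. The sample size is not at issue.

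**2. What the label does to one patient.** Take 20 planned sessions and a patient who attended 6 of the first 8 and then stopped.

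| Label and rule | Rate |
|---|---|
| Unplanned | 6/20 = 0.30 |
| Planned, Outcomes section of the Methods | 20/20 = 1.00 |
| Planned, statistical Outcomes section | 6/8 = 0.75 |

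The label raises the rate under either rule. It makes it 1 only under the first, unless no session was missed before n.

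**3. Shift in the arm difference with no true effect.**

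Shift in sessions = 20 × (share of early leavers) × (difference between arms in the proportion labelled planned) × (rate if planned − rate if unplanned).

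- From the article: 64 per arm, 20 sessions, and 23.9% early leavers (the dropout figure it cites for eating disorders).
- Assumed: leavers average 40% attendance and completers 85%; a planned leaver scores 1 under the first rule and about 0.85 under the second (85% attendance before stopping); 20% of control leavers are labelled planned.

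First rule: 20 × 0.239 × 0.60 = 2.87 sessions per unit of labelling difference. Second rule: 20 × 0.239 × 0.45 = 2.15.

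**4. Type I error.** Simulation with 8,000 replicates per scenario and a t-test on the rate. Leavers' rates are drawn with mean 0.40 and SD 0.20, completers' with mean 0.85 and SD 0.12, both limited to 0–1.

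| Planned, control v experimental | Shift, first rule | Type I error, first rule | Shift, second rule | Type I error, second rule |
|---|---|---|---|---|
| 20% v 20% | 0 | about 5% | 0 | about 5% |
| 20% v 40% | 2.87 × 0.2 = 0.57 | about 12% | 2.15 × 0.2 = 0.43 | about 9% |
| 20% v 50% | 2.87 × 0.3 = 0.86 | about 21% | 2.15 × 0.3 = 0.65 | about 14% |
| 20% v 70% | 2.87 × 0.5 = 1.43 | about 53% | 2.15 × 0.5 = 1.08 | about 35% |

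**5. Sensitivity to the assumptions.**

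- *More leavers.* At 45% (assumed), 20% v 40% gives about 21% under the first rule and 15% under the second.
- *Larger spread.* The simulated population has a mean of about 14.8 and an SD of about 4.6 sessions; the article reports 13.58 and 5.82 and plans on 6. With SD 6, the standard error is 6 × √(2/64) = 1.06, and the first-rule shifts give about 8%, 13% and 27% (normal approximation).
- *Planned type of model.* A Poisson model with a log(planned) offset and robust errors gave 13%, 21% and 53% under the first rule and 9%, 13% and 31% under the second, with 23.9% leavers.

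**The case against.** The strongest reply is that the authors saw this coming. The blinded assessor is introduced for the very case of therapists judging withdrawal, and the task includes a file check as well as a count. If that check is an independent, blinded decision on planned versus unplanned, much of the risk goes. That would be a real safeguard, but the article does not say so, and the statistical section still gives the decision to the therapists. What stands is that the assessor's authority is unclear, not that the risk was ignored.

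Four stronger readings are tempting, and the documents do not support them.

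- **The bias favours feedback.** Allegiance points that way, but the feedback arm also shows off-track alerts, which could make therapists less ready to call an ending agreed. No labelling rates are given.
- **The label turns every dropout into full attendance.** This holds only under the Methods rule.
- **Labelling could account for the whole planned effect.** Under the first rule with 23.9% leavers, a 3-session shift needs a labelling difference of 3/2.87 = 1.05, which is impossible. With 45% leavers it needs 3/(20 × 0.45 × 0.60) = 0.56.
- **No analysis without the label is planned.** The full protocol and analysis plan are not shown, so this cannot be said.

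It is also fair that the cited 23.9% describes patients who choose to leave, not every early ending open to relabelling, so the illustration's base is approximate.

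**Conclusion.** The point holds as a weakness in a stated rule. The planned/unplanned decision changes the primary outcome, it rests with therapists who know the arm and expect feedback to help, and the described safeguard is not said to reach it. Differential labelling is a possibility; nothing shows that it occurs.

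In the illustration, a 20-point labelling difference raises type I error from 5% to roughly 9–12%, and a 50-point difference to roughly 35–53%, depending on which scoring rule applies. These figures rest on assumed attendance levels and labelling rates. A larger SD lowers them and more leavers raise them. This should be corrected, but it does not by itself invalidate the design.

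**What to change.** 1. **Who decides.** State that the existing blinded assessor makes the final planned/unplanned classification, from withdrawal reasons with arm information masked, under criteria set in advance. The cost is a modest extra task and the masking of file extracts while recruitment is under way. It reduces the bias but does not remove it, because therapists still write the reasons.
2. **Sensitivity analysis.** Pre-specify sessions actually attended over the original 20 or 25, with nobody recoded, and report planned and unplanned withdrawals by arm. The drawback is that genuine early completers count as low attenders. The analysis therefore supports interpretation and is not a condition for claiming better attendance.
3. **Reconcile the text.** Choose one scoring rule for a planned early ending, since the two Outcomes sections differ, and make it cover patients with 25 planned sessions as well as the n below 20 case. Align the section on randomization and blinding with the Discussion on whether attendance is assessed blind. This costs wording only.

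The sample size is unchanged.

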### Missing values

Missing values of the secondary outcome and/or covariates included in its analysis are imputed using multiple imputation (SPSS), if the percent of missing patients is >5% and *P* of Little’s test is <5%. The result of the analysis of the imputed datasets is then the primary result.

The assumption of multiple imputation is that the data are missing at random, i.e., that for a given quantity with missing values, the distribution of observed values of this quantity conditional on values observed of other quantities is the same as the conditional distribution of the values planned to be observed of the quantity, but missing. If this condition is not fulfilled, the results of the multiple imputation will be biased. To obtain the range of plausible bias that may result if the MAR (missing at random) condition is not fulfilled, we will do the following two analyses using single imputations of the outcome performed as a sensitivity analysis: 1) missing values in group A are imputed by the minimum value observed in the material, while missing values in group B are imputed by the maximum value observed, and the two groups are compared; and 2) vice versa.

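### The Mann-Whitney fallback for continuous outcomes cannot yield the covariate-adjusted result that the same section defines as primary, so the primary EDE result is ambiguous if it is used

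*Protocol article*

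**What the plan says.** The relevant rules stand in two consecutive paragraphs of the protocol article, in the Outcomes section under Statistical analysis plan.

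- First paragraph: "In the analysis of continuous outcomes the univariate general linear model is used". It is followed directly by the fallback: "If the assumptions of a regression are not fulfilled, a non-parametric test is used (Mann-Whitney".
- Second paragraph: "All outcomes are analyzed using regression analyses, including the binary intervention indicator", and then "The primary results are those adjusted by the protocol-specified stratification variables and (where measured) the baseline value as covariates".

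Other sections fix what these rules act on.

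- Randomization and blinding: "The randomization is stratified for eating disorder diagnosis (BN, EDNOS or BED) and treatment type (basic or elaborate". These are the covariates meant by the adjustment rule.
- Outcomes (in the description of measures): "The secondary outcome is the global score of eating disorder examination (EDE) interview, assessed at the end of intervention". The sentence after it says that group means are compared.
- Table 2 shows EDE at the trial assessment, so a baseline value exists and the baseline part of the rule applies.
- Table 3 sets a minimal relevant EDE difference of 0.5 points with SD 1.33, and power of 55.9% (N = 128) or 68.3% (N = 170).
- Missing values: if more than 5% of patients have missing data and Little's test gives P below 5%, multiple imputation is used for the secondary outcome, and "The result of the analysis of the imputed datasets is then the primary result".
- Statistical analysis plan and Multiplicity: analysis is blinded with arms labelled A and B, and EDE is tested only if the attendance test is significant.

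**The concern.** The fallback and the adjustment rule cannot both be followed. A Mann-Whitney test compares two samples by rank. It has no place for diagnosis, treatment type or baseline EDE, and it does not estimate a difference in means. If the fallback is used, three things change together: the covariates are dropped, the target moves from an adjusted mean difference to an unadjusted rank comparison, and the 0.5-point yardstick in Table 3 no longer applies. The article does not say whether the rank test then replaces the adjusted result as primary or stands beside it.

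This matters most for EDE, the one secondary outcome in the fixed testing order. The two analyses can disagree on significance, so a reader of the final report could not tell from the article which one decides the claim. If the imputation rule is also triggered, the article gives no way to combine a rank result over the imputed datasets.

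**Working it through.** **Inputs.** From the article: difference d = 0.5, SD s = 1.33, two-sided 5% level, n = 64 or 85 per arm. Assumed: the correlation r between baseline and final EDE, which the article does not give, taken as 0.3, 0.5 and 0.7.

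**Step 1, reproduce Table 3.** Two-sample t-test with noncentrality d / (s·√(2/n)).
- n = 64: 0.5 / (1.33 × 0.1768) = 2.13, power 56.0% (stated 55.9%).
- n = 85: 0.5 / (1.33 × 0.1534) = 2.45, power 68.3% (stated 68.3%).

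The stated power is therefore for an unadjusted comparison.

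**Step 2, Mann-Whitney under normality.** Relative efficiency 3/π = 0.955, so 64 per arm acts like 61.1 and 85 like 81.2. Power is about 54% and 66%, roughly 2 points below Table 3.

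**Step 3, the baseline-adjusted model.** Residual SD = 1.33·√(1 − r²).

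| r | Residual SD | Power, n = 64 | Power, n = 85 |
|---|---|---|---|
| 0.3 | 1.27 | 60.0% | 72.4% |
| 0.5 | 1.15 | 68.3% | 80.3% |
| 0.7 | 0.95 | 84.0% | 92.7% |

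**Step 4, skewed scores, where the fallback would act.** Simulation of 3,000 trials per cell: outcome = 1.33·(r·baseline + √(1 − r²)·error) minus 0.5 in one arm, with normal baseline and centred, scaled gamma errors (shape 2). The article names no assumption check, so a Shapiro-Wilk test of the residuals at 5% was assumed. It failed in all of these skewed trials. At n = 64:

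| r | Adjusted linear model | Mann-Whitney | Trials where the two verdicts differ |
|---|---|---|---|
| 0.3 | 59.3% | 67.1% | 16.9% |
| 0.5 | 68.0% | 60.7% | 20.7% |
| 0.7 | 83.0% | 57.2% | 32.3% |

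The table uses ordinary standard errors. A separate skewed simulation with HC3 standard errors gave 59% v 70%, 67% v 63% and 83% v 57% at the same correlations. Another, with gamma shape 3, gave 60% v 65% at r = 0.3, 69% v 67% at 0.5 and 73% v 66% at 0.6. So the Mann-Whitney loss at r = 0.5 ranges from 2 to 7 points with the assumed shape, and its gain at r = 0.3 from 5 to 11 points.

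**Step 5, type I error at n = 64.** The two-stage rule (check, then choose the test) gave 4.3% to 5.8% across normal and skewed cells. The Monte Carlo standard error is √(0.05 × 0.95 / 3,000) = 0.4 points. The HC3-adjusted model gave 4.2% to 5.2%.

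**Step 6, pooling.** The Mann-Whitney probability index with a DeLong variance was combined by Rubin's rules (20 imputations, about 20% missing at random, normal errors, r = 0.5, 1,500 trials). Type I error was 5.1% and power 48%.

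**Limit.** These simulations adjust for baseline only. The effect of dropping the stratification variables is not quantified.

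**The case against.** Several points on the other side are sound.

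- The fallback test is named in advance, the arms are coded A and B, and EDE is tested only after a significant attendance result. A reader might infer that the test would be picked to suit the result. The documents do not support that: coding hides the direction of effect (although P values stay visible), and step 5 shows no material error inflation.
- A reader might infer that a rank result cannot be pooled, and so that the fallback contradicts the imputation rule. It does not. A rank-based estimate with a standard error can be pooled, as step 6 shows. The article simply gives no method, and the question arises only if both imputation conditions are met.
- A reader might quote the large power gaps for symmetric scores. There the regression assumptions hold and the linear model would normally be kept, so those gaps do not measure the fallback.
- Against the article's own stated power, the cost is only about 2 points under normality. The larger losses are against the adjusted analysis and rest on an assumed correlation.
- The diagnostic and its threshold are details that an article may leave to a full analysis plan, so their absence is not counted here.

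What does not fall away is the conflict between two rules that the article states outright. More detail on the check would not resolve it, because a plain Mann-Whitney test cannot give an adjusted result whatever triggers it.

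**Conclusion.** The point holds as a conflict of rules. If the fallback is used, the article's definition of the primary result for continuous outcomes cannot be met, the EDE comparison stops being one of means, and it is unclear which result counts. In the skewed setting of step 4, the adjusted model and Mann-Whitney disagreed on significance in 17% to 32% of trials with a true 0.5-point difference, so the ambiguity can decide the EDE conclusion.

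The effect on power depends on the baseline correlation. With skewed scores at 64 per arm, Mann-Whitney loses a little at about 0.5 (2 to 7 points), loses much at 0.7 (about 26 points), and gains at 0.3 (5 to 11 points). No type I error inflation was found. These sizes rest on the assumed correlations, the assumed gamma shapes and, for the two-stage rule, the assumed check. The rule conflict rests on none of them.

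**What to change.** Replace the fallback sentence. Keep the linear model adjusted for baseline and stratification variables as the primary analysis of every continuous outcome, with heteroscedasticity-robust (HC3) or bootstrap standard errors if residuals are non-normal or unequal in variance. Make any rank test a sensitivity analysis, preferably one that adjusts for both baseline and strata, such as rank ANCOVA. A rank test stratified only by diagnosis and treatment type would still omit baseline.

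This keeps one estimand, matches the mean comparison and the 0.5-point difference, and gives an estimate and standard error that combine directly over imputed datasets. Robust standard errors do not correct a wrong shape for the relation with baseline, so that should still be looked at.

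The cost is one sentence, plus some lost power if EDE scores prove strongly skewed and weakly related to baseline (5 to 11 points in the simulations at a correlation of 0.3).
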